## Abstract

**Background:**

Due to the gradual loss of function, it is crucial for persons with dementia to discuss advance care planning in due course. However, nursing home staff, residents and their families feel uncomfortable to start this type of conversation, resulting in unknown (care) preferences. ‘We DECide optimized’ will provide tools to nursing home staff for discussing advance care planning. The primary objective is to enhance the level of shared decision-making in advance care planning conversations. We hypothesize that the training will enhance the perception of the importance, competence and frequency in which participants engage in advance care planning conversations. The secondary objective is to assess barriers and facilitators in the implementation of advance care planning policies at the ward level.

**Methods:**

‘We DECide optimized’ will consist of two four-hour workshops and a homework assignment between sessions. Training components will include information on advance care planning and shared decision-making, role-play exercises and group discussions on implementation barriers at the ward level. Participating wards will receive supporting materials to stimulate residents and their families to initiate conversations. The study uses a cluster randomized controlled design, with 65 Flemish nursing home wards taking part (311 staff members). Data will be collected through a pretest-posttest model, with measurements up to 9 months after training. The RE-AIM framework will be used to evaluate the effectiveness of the implementation. Quantitative and qualitative data at the clinical, organizational and resident level will be collected.

**Discussion:**

This study describes a hands-on, in-depth and multi-level training approach to improve shared decision-making in advance care planning conversations. By providing tools to ward staff, engaging the management and informing residents and their families, ‘We DECide optimized’ aims to decrease evidence-based barriers and to provide all stakeholders with incentives to engage in conversations about (care) preferences in an informative and participatory manner.

**Electronic supplementary material:**

The online version of this article (10.1186/s12877-019-1044-z) contains supplementary material, which is available to authorized users.

## Background

Approximately 50 million people worldwide live with dementia [1]. In Flanders (Belgium), 114,000 persons are affected by the syndrome, and this figure is expected to double by 2060 [2]. 65.9% of people with dementia above the age of 65 die in a nursing home [3, 4]. Due to the gradual loss of (cognitive) function and the fact that approximately 71% of persons with advanced stages of dementia die within 6 months of admission, it is imperative that nursing homes record a person’s (care) preferences in a timely and well-documented manner [5, 6]. Advance care planning enables this policy.

Advance care planning (ACP) allows individuals to define goals and preferences for future medical treatment and care, to discuss these goals and preferences with family and health-care providers, and to record and review these preferences as and where appropriate [7]. Involving persons and their families in the decision-making of care preferences is considered a pivotal element in person-centered care. [8]. However, a 2014 nationwide retrospective study reported that only 11.8% of persons with dementia expressed their wishes regarding end-of-life care in nursing homes [9]. Both nursing home staff and residents and their families express apprehensions in initiating ACP. Health professionals usually refrain from taking responsibility because there is no task agreement on ACP at either the ward or the organizational level [10]. They also find it difficult to converse with people living with dementia about their (end-of-life) care preferences [11]. Meanwhile, residents and families lack information on ACP and its benefits [12].

Communication regarding care preferences is also rarely patient driven in nursing homes, which acts as an additional barrier to engage in ACP [9, 13]. This ‘paternalistic’ approach runs contrary to the principles of shared decision-making (SDM), which require the active involvement of persons and their families in care and treatment decisions [14]. The three-talk model for SDM as proposed by Glyn Elwyn and colleagues translates the theoretical concept into a guided approach for clinical practice [15]. The three steps are: (1) making sure that people know that multiple options are available (Choice Talk); (2) providing detailed information about these choices (Option Talk); and (3) considering preferences and working towards a decision (Decision Talk). A recent revision substitutes Choice Talk with Team Talk to depict better the process of collaboration and deliberation between conversation parties [16].

Based on the barriers listed above, Kononovas & McGee propose 4 steps to improve the quality and uptake of ACP [17]. These are: (1) taking steps to inform and empower patients; (2) putting better systems in place; (3) taking responsibility for initiating discussions; and (4) ensuring health professionals have the right skills. Training care professionals in the use of SDM, while simultaneously engaging management, residents and their families, can thus serve as a means to facilitate ACP [11, 18]. It is however necessary that all those involved acknowledge the complex and time pressured environment in which nursing homes operate [19]. Taking these considerations into account, we developed ‘We DECide’ (We Discuss End-of-life Choices), a communication training program for nursing home staff to facilitate SDM in ACP conversations with residents and their families. The three-talk model for SDM guided the development and assessment of the intervention.

A feasibility study was conducted with ‘We DECide’ between 2010 and 2014 in 19 Flemish nursing wards [20]. Focusing on training in communication skills and empowering nursing home staff from different backgrounds to initiate ACP discussions, the intervention showed promising results in improving the competence of participants when using SDM, but did not improve the actual use of SDM in observed conversations [21, 22]. Based on qualitative feedback from participants and on recent literature, additional focus on the organizational level of ACP and the involvement of all SDM stakeholders, including residents and their families, was added to the training [23]. There were no changes to existing training components, though some training materials which were found to be too time-consuming, were reworked into more accessible editions. The revised intervention was named ‘We DECide optimized’.

### Aims

The primary goal of ‘We DECide optimized’ is to enhance the level of SDM in ACP conversations. In order to achieve this goal, we set 4 objectives. (1) At the clinical level, participants need to receive training in communication skills to enhance the frequency and competence with which they use SDM. (2) Participants from all backgrounds need to be invited to the training program, including management and non-healthcare professionals, in order to engage all professionals of the ward in initiating ACP. (3) At the organizational level, wards need to be given the opportunity and guidance to reflect on their ACP policy, including the use of SDM. (4) At the resident level, persons with dementia and their families need to be enticed to engage in ACP discussions and be given the tools to do so.

The secondary goal of ‘We DECide optimized’ is to assess barriers and facilitators in the long-term implementation of ACP policies based on the use of SDM in nursing homes. By engaging professionals both at the clinical and organizational level, as well as the residents themselves, we will receive quantitative and qualitative feedback from multiple stakeholders to improve person-centered care as well as future interventions. Since advance care planning is both an individual and a team-based effort, we opted for a cluster randomized controlled design to assess objectives at both the participant and the ward level.

Our hypotheses are as follows. ‘We DECide optimized’ will increase the level of SDM in ACP discussions. The training will enhance the perception of the importance, competence and frequency in which participants engage in ACP conversations. After a period of 3–9 months of implementing what was learned during the training, these changes will be firmly integrated at the ward level and into the general policy. Both staff and management play an important role in stimulating these changes, with the latter actively supporting the implementation and the use of SDM in ACP discussions after undergoing the training. Residents and their families will feel more involved in expressing their wishes and preferences through our information campaign (see below).

## Methods

### Intervention design

‘We DECide optimized’ is a training program for nursing home staff. Nursing homes participate per ward with both professionals and members of management. The training will consist of 2 workshops of 4 h each, with a homework assignment between sessions. Two trainers, one with a background in psychology and the other in nursing, and each with over 25 years of career experience in holding SDM & ACP conversations in nursing homes, will conduct the training sessions. One of the authors (BG) will be present as well to oversee the research component of the intervention.

The training will consist of 3 modules which pertain to both the participant and the ward level. These are: (1) a theoretical introduction to ACP & SDM, (2) role play exercises and (3) reflecting on ACP policy. All wards will also receive supporting materials to stimulate residents and their families in participating in ACP conversations at the end of the first workshop. These modules are described below (Fig. 1. Intervention modules).

**Fig. 1 Fig1:**
[figure not shown]
Intervention modules

### Workshop 1

Participants will first receive a theoretical introduction on SDM and ACP which outlines the concepts and addresses several misconceptions, such as ACP being only a part of palliative care. The importance of a multi-level approach at the clinical, organizational and resident levels will be stressed. Due to the differing backgrounds of our participants, it is important to establish a common ground from which to work on. This module will take about 1 hour.

We will then introduce the main focus of the training, namely Elwyn’s three-step talk model and discuss the importance of a structured approach to ACP discussions based on SDM [15]. To facilitate the uptake of this information, all participants will be issued a brief card with 12 pointers which summarize Choice Talk, Option Talk and Decision Talk (Fig. 2. Pointers for discussing ACP). After the introduction and discussion of this training method, a role-play exercise will be introduced to begin hands-on training. It is important to note that each role-play exercise in ‘We DECide optimized’ focuses on a critical moment to discuss ACP: at the time of admission, during daily informal conversations and during crisis situations. Since the focus on certain conversation elements changes depending on the time of conversation (working towards a decision will be more important during crisis situations than during the time of admission, for instance), participants will practice the three-step talk model in different situations. The first role-play exercise will focus on a conversation at the time of admission. Participants will take part in the exercise by either re-enacting a case, or by fulfilling predefined observation tasks. Each case will include the role of a person with dementia to ensure that the conversations are tailored to their needs. All cases, roles and tasks for the exercises were adopted from ‘We DECide’ [20]. The trainer will guide the exercise by means of the brief card and will address communication pitfalls as well. At the end there will be a discussion on lessons learned. This portion of the workshop will take about two and a half hours with a brief pause in between. The final half hour of the workshop will introduce information about the homework assignment as well as the information campaign. Wards will also receive a poster of the three-talk step model to introduce and discuss with other colleagues. All materials are designed to be easily disseminated.

**Fig. 2 Fig2:**
[figure not shown]
Pointers for discussing Advance Care Planning

### Homework assignment

In the 4 weeks between the two workshops, participants will practice the different steps of the three-step talk model by engaging in at least one informal conversation with a resident living with dementia and/or family. It is important to note that residents or families often implicitly or explicitly express preferences or fears concerning the daily routine in the nursing home ward, for example when another resident becomes ill. Continuously observing and taking these opportunities to talk are important for keeping abreast of the concerns and wishes of the ward population. These moments can also serve as a signal for a formal ACP conversation. Participants are instructed to write down their experiences and list a number of barriers and facilitators which might have hindered or helped the conversation. These homework cases will then be sent in 1 week before workshop 2, during which they will be summarized by the trainer and then discussed during workshop 2. Since this discussion will contain a summary of all barriers and facilitators which were encountered by the group as a whole, the training will not be affected if a participant was unable to do the homework assignment. Reasons for not being able to complete the assignment will be noted, though the participant will not be barred from workshop 2.

### Workshop 2

The homework assignments will be discussed during the first hour of the second workshop. Participants will reflect on their conversations and offer each other suggestions on how to improve their communication skills. This information will be noted by BG as part of his task to oversee the research component of the intervention. Another role play exercise will be introduced during the second hour. It will focus on ACP conversations in crisis situations. If participants have not re-enacted a case during workshop 1, they will be invited to take up a role. At the end, there will be a discussion about lessons learned. Both segments are to be assisted by the trainer. After a short break, participants will be invited to sit down with their other staff members to discuss their ACP policy. They will be asked to list a number of opportunities and ways to improve their policy in a period of 3 to 9 months. Recommendations to achieve person-centered care will be given on a single page document to assist them in this task. This document is based on the ACP Guidelines which were previously used in ‘We DECide’, but were found to be too cumbersome and time-consuming [20]. After 1 hour, both wards will come together again to discuss their opportunities for improvement. The trainer and other ward members will give recommendations for improving the achievability of these ideas. The wards will be contacted in 3 and in 9 months to check progress on their objectives and to provide further incentives for improving their policy. This discussion will last 30 min. During the last half hour, participants will fill in the IFC-SDM questionnaire, which assesses the competence, importance and frequency at which staff members engage in SDM (see also: IFC-SDM). They will also fill in an evaluation form concerning their experiences during both workshops and the homework assignment. Details on post-training measurements and follow-up interviews will be discussed.

### Supporting materials

*Presentation.* Both workshops are guided by a PowerPoint presentation.*Brief card.* Lists 12 OPTION-based pointers for the use of SDM in ACP conversations.*A4 document.* Lists 10 recommendations to achieve person-centered care.

### Information campaign

In order to stimulate residents with dementia and their families to participate in ACP conversations, we developed an information campaign in collaboration with the nursing home Huis Perrekes. The title of the campaign is: ‘Shared Decision-Making. Your choice, our care.’ Participating wards will receive multiple copies of these supporting materials at the end of the first workshop. They will be able to provide feedback during the second workshop and during the telephone interviews in 3 and 9 months. Feedback from residents and their families will be gathered at the same time by means of ad hoc forms. The materials are:

### Poster

Two A2-size posters depicting the title of the campaign and the image *Heaven* will be given to participating wards to hang up at key locations, such as the elevator or cafeteria. *Heaven* features a collective knot work of bleached, re-used textiles in different colors. It is made by a collective of residents, children and volunteers to underscore that ACP is a team effort. The poster also invites residents and their families to participate in SDM by talking to their caregivers about it. The image and text are restricted to a minimum in order to not confound persons with dementia or their families with too much information. It is intended to raise questions and initiate conversations.

### Pocket card

30 A6-size pocket cards will be distributed to each ward. These pocket cards prepare residents and their families for an ACP conversation by inviting them to ask 3 questions: (1) What are my options? (2) What are the (dis)advantages of every option? (3) What do I need to make a decision? These 3 questions were adopted from the corresponding article by Shepherd et al. [24].

### Information page

30 A4-size information pages will be handed out to each ward. The pages contain information about SDM, including the three-step talk model, and invite residents and families to reflect upon their care preferences and to request information actively. They are designed to work in tandem with the pocket cards, but can also be used exclusively. Both the information pages and the pocket cards can be put to use in different ways, e.g. to provide information upon admission, in preparation of a formal ACP conversation or as part of an ACP awareness campaign. In this way, we make sure the material can be operationalized in nursing homes with different cultures and approaches to information distribution.

### Study design

The study uses a cluster randomized controlled design, with clusters at the ward level. ‘We DECide optimized’ will be implemented in the intervention group, while the control group receives no training. After all measurements have been simultaneously conducted in both groups, excluding the interviews regarding long-term implementation results, the control group will receive training as well. Data will be collected through a pretest-posttest model, with measurements at 5 time points. These are (T0) 3 months prior to training, (T1) directly after the last training session, (T2) 3 months after training, (T3) 6 months after training and (T4) 9 months after training (Fig. 3. Study overview).

**Fig. 3 Fig3:**
[figure not shown]
Study overview: time points, levels of measurement and assessment instruments

This study will report pretest-posttest results by means of the RE-AIM Framework [25]. This model can be used to plan and evaluate public health interventions through the assessment of 5 dimensions: Reach, Effectiveness, Adoption, Implementation and Maintenance (Table 1. RE-AIM dimensions). These dimensions can occur at multiple levels, such as the clinical or organizational level, and thus corresponds to the current study. It is also specifically useful for interventions such as ‘We DECide optimized’, which focus on behavioral change, the assessment of implementation barriers and facilitators and external validity [26].

**Table 1 Tab1:** RE-AIM dimensions [26]

Dimension	
Reach	Number, percentage and representativeness of patients who participated in the intervention.
Effectiveness	Intervention effects on targeted outcomes.
Adoption	Number, percentage and representativeness of participating settings and providers.
Implementation	The extent to which the intervention was consistently implemented by staff members.
Maintenance	The extent to which the intervention becomes part of routine organizational practices, and maintains effectiveness.

### Required sample size

The required sample size is calculated through the clusterPower software package for R, which takes the cluster-randomized design of the study into account [27]. Using a power of 0.80, assuming unequal cluster sizes (x̄=5, σ_X_ = 1) and an intraclass correlation of 0, a sample of 32 nursing home wards per condition is needed at the 5% significance level.

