### Settings/participants

Participation calls were sent out by e-mail to the 4 major umbrella organizations for nursing homes. To maximize sample size, each of the 755 Flemish nursing homes was also individually contacted by means of a flyer. Enrollment was voluntarily, albeit 5 inclusion criteria needed to be met. These were: (1) The ward unit must be focused on persons with dementia, or at least have a mixed population. (2) A minimum of 4 to a maximum of 6 ward staff members can participate. (3) At least one of these members must stem from either middle or executive management. This person must be directly involved with the participating ward (e.g. work there or coordinate tasks) and delegate all information and assessment requirements to the other members. These other participants can be either care or non-care professionals as long as they interact with the residents and their families on a regular basis. (4) Enlisting wards enroll in both the training as well as the research module. (5) The nursing home has not participated in ‘We DECide’, and will not participate in other ACP research for the duration of the training.

One hundred ninety nursing homes responded to the flyer, whereupon they received more information. Forty-eight of these 190 nursing homes subscribed for a total of 65 wards (311 participants). The primary reasons for not participating in the study were resistance from management or staff members, reluctance to send in audio files (see also: OPTION) and the long-term duration of the intervention. We also received a lot of interest from psychiatric wards, which we unfortunately had to decline because the intervention was not tailored to the specific population.

BG distributed the 65 nursing home wards in the intervention and control group through simple randomization in Excel before any measurements were conducted. The randomization was conducted at the nursing home level (48) at a 1:1 ratio to avoid contamination between clusters in a single nursing home. This resulted in 34 wards in the intervention group and 31 wards in the control group. Clusters, participants and trainers were blinded of group assignment (single-blind trial). Participants completed written informed consent forms upon enrollment before the randomization.

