### Statistical analysis

Due to the cluster-randomized design of the study, longitudinal multilevel analysis (linear mixed modeling with random intercepts at both the clinical and the ward level) is used as the method of analysis. Since nursing homes can participate in the training with multiple wards, an additional organizational level is added as well. SPSS 25 is used for the analysis.

First, the effectiveness of ‘We DECide optimized’ on the primary outcome – the use of SDM in ACP conversations – is assessed. Second, the effectiveness of the training on the secondary outcomes – (1) self-perceived importance, competence and the use of SDM in ACP conversations, (2) ACP policy and (3) support from management – is examined. Separate analyses assess whether our demographic variables influence the primary outcome. Only significant predictors are added to the final model.

Differences in baseline characteristics between the intervention and control group are analyzed by descriptive analysis.

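### The sample size is said to allow for clustering but sets the intraclass correlation to 0, counts wards although homes were randomised, and assumes 5 observations per ward where OPTION-12 has 2

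*Protocol article*

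**What the plan says.** The Required sample size section uses a software package "which takes the cluster-randomized design of the study into account". It enters power 0.80 and ward sizes with mean 5 and standard deviation 1, and with "an intraclass correlation of 0, a sample of 32 nursing home wards per condition is needed at the 5% significance level". It gives no reason for the 0, and it does not name the outcome, the effect size, the standard deviation or whether the test is one- or two-sided.

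Other sections describe the design differently:

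- Study design describes a cluster randomised trial "with clusters at the ward level".
- Settings/participants reports 48 homes, 65 wards and 311 participants, and says: "The randomization was conducted at the nursing home level (48) at a 1:1 ratio". The stated reason is contamination between wards of one home. "This resulted in 34 wards in the intervention group and 31 wards in the control group".
- Statistical analysis plans random intercepts at the clinical and ward levels, and then: "Since nursing homes can participate in the training with multiple wards, an additional organizational level is added as well".
- Primary outcomes says each ward sends in 2 recordings for OPTION-12 at pretest, 3 months and 6 months. The SDM-Q and collaboRATE forms accompany those conversations.

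**The concern.** A method cannot allow for clustering while the one parameter that carries clustering is set to 0. The stated variation in ward size then has no effect either. The sample size section also uses a unit (the ward) that was not the unit randomised, and a number of observations per ward (5) that fits the staff questionnaires, which are secondary outcomes, rather than the recorded conversations.

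What is at stake is how a null result is read. The 80% is the only benchmark the article gives for the trial's sensitivity. If outcomes are correlated within wards or homes, the planned mixed model will give wider intervals than this calculation allowed for, and a null result would look more conclusive than it is. The Background reports that the feasibility study did not improve the actual use of shared decision-making in observed conversations, so a null result on the primary outcome is a realistic possibility.

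**Working it through.** **Inputs from the article.** Power 0.80; 5% level (two-sided assumed); 32 wards per arm; ward size mean 5, SD 1, so CV = 1/5 = 0.2; ICC 0. Enrolled: 48 homes, 65 wards (34 and 31), 311 participants, hence 311/65 = 4.78 per ward and 311/48 = 6.48 per home. OPTION-12: 2 recordings per ward per time point. Every non-zero ICC below is an assumption.

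**1. The stated figure.** The 32 cannot be reproduced forwards without an effect size, so I solved for the standardised difference d that makes it true. With 32 × 5 = 160 per arm and ICC 0, the normal approximation gives d = (1.960 + 0.842) × √(2/160) = 0.313. A t test with 62 df gives d = 0.318. (A one-sided 5% test would give 0.278.) I use 0.318.

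**2. Design effect.** DE = 1 + ((1 + CV²)m − 1) × ICC. With m = 5 and CV = 0.2 this is 1 + (1.04 × 5 − 1) × ICC = 1 + 4.2 × ICC. At ICC 0 it equals 1 whatever the CV, so the calculation is that of an individually randomised trial with 160 per arm.

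**3. Power at d = 0.318 with clusters of about 5 per ward.** By ward: 160 per arm, 62 df. By home: enrolled sample, arms of 34 × 4.78 = 163 and 31 × 4.78 = 148, DE = 1 + (6.48 − 1) × ICC, 46 df. Wards needed are 32 × DE, rounded up. The detectable d is 0.318 × √DE.

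| Assumed ICC | DE, ward | Power, 32 wards/arm | Wards/arm for 80% | Detectable d at 80%, 32 wards/arm | DE, home | Power, enrolled, by home |
|---|---|---|---|---|---|---|
| 0 | 1.00 | 80% | 32 | 0.318 | 1.00 | 78% |
| 0.01 | 1.04 | 78% | 34 | 0.325 | 1.05 | 76% |
| 0.05 | 1.21 | 72% | 39 | 0.350 | 1.27 | 68% |
| 0.10 | 1.42 | 65% | 46 | 0.379 | 1.55 | 60% |
| 0.20 | 1.84 | 54% | 59 | 0.432 | 2.10 | 47% |

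The number of homes per arm is not given. Assuming 24 per arm with CV 0.2 instead gives about 68%, 59% and 47% at ICC 0.05, 0.10 and 0.20.

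**4. Two recordings per ward.** 32 × 2 = 64 recordings per arm.

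- At d = 0.318 and ICC 0, power is about 43%.
- To isolate the effect of the ICC, re-solve for 80% at ICC 0, which gives d = 0.503. With DE = 1 + (2 − 1) × ICC, that is 1.05, 1.10 and 1.20, power is 78%, 76% and 72% at ICC 0.05, 0.10 and 0.20.
- By home, 65 × 2 = 130 recordings over 48 homes is 2.71 per home. With DE = 1 + 1.71 × ICC and 46 df, power is 77%, 74% and 68%.

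For the recordings, then, the number of observations matters more than the ICC.

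**5. The enrolled ward split.** 34 and 31 wards at 4.78 per ward, ICC 0, clustered by ward: 78.8%.

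**The case against.** The strongest reply is that the article does not hide its assumption: the ICC is printed in the same sentence as the result, 80% is an input, and the planned analysis has random intercepts at ward and organizational level, so the inference itself allows for clustering. That stands. The fault lies in the sample size justification, not in the test or its intervals.

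A reader might infer four stronger things that the article does not support.

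- **That the trial's true power is some particular figure well below 80%.** No ICC or effect size is given. The loss is under 2 percentage points by ward at ICC 0.01. The design also has a pretest and repeated measures. As an illustration, adjusting for a baseline with an assumed correlation of 0.5 multiplies the variance by 0.75 and, at d = 0.318 with clusters of 5, gives about 84% at ICC 0.05 and between 77% and 78% at 0.10. The sample size section invokes none of this, so it does not rescue the stated basis, but it rules out naming one delivered power.
- **That randomising by home contradicts ICC 0.** Contamination is spill-over of training between wards, which is a different matter from correlated outcomes. Likewise, random intercepts allow for correlation without asserting it.
- **That the control arm's 31 wards against 32 is a material shortfall.** The total is 65 against 64, and power at ICC 0 is 78.8%.
- **That the article conceals the unit of randomisation.** Settings/participants states it plainly; only Study design and the sample size count are out of line. At ICC 0 the choice of unit hardly matters (about 78%).

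**Conclusion.** The point holds as a fault in the stated basis of the sample size. The claim to allow for clustering is incompatible with an unjustified ICC of 0, and any positive ICC takes power below 80% on that section's own inputs. The size of the loss is conditional. With about 5 observations per ward it runs from 2 to 26 points by ward over ICC 0.01 to 0.20, and home-level clustering lowers the enrolled sample's power to between 76% and 47%. With 2 recordings per ward the ICC alone costs about 2 to 8 points by ward over 0.05 to 0.20, but a difference of 0.32 would have only about 43% power before any clustering. These figures rest on a two-sided 5% test, a back-solved d, assumed ICCs and a single-time-point comparison without baseline adjustment.

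**What to change.** Change the Required sample size section as follows, without enrolling more wards:

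- Withdraw ICC 0 as the basis for the 80% figure.
- State the outcome, the effect size and the observations per ward behind the 32. Without these no power figure can be restated.
- Report power, or the minimum detectable difference, for the enrolled 48 homes and 65 wards over a non-zero ICC range (for example 0.01 to 0.20), with clustering at both home and ward level. Use the 19-ward feasibility data if an ICC can be estimated from them. Take credit for baseline adjustment or repeated measures only if the assumed correlation is stated.
- Do this for OPTION-12 with 2 recordings per ward, separately from outcomes with about 5 respondents per ward.

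In Study design, describe the trial as randomised by nursing home, with wards nested within homes.

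The cost is a short recalculation and some rewording. Enrolment, randomisation and the analysis model are unchanged, but the stated power will probably be less favourable.
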